**1. Introduction to Application**

This is a revision of an R01 application that was initially submitted September 7, 2007 and was re-submitted January 8, 2008. The overarching goal of this project is to define the natural history and clinical significance of transmitted low-frequency human immunodeficiency virus type 1 (HIV-1) drug resistance mutations using the oligonucleotide ligation assay, OLA.

The Summary of Discussion from March 5, 2008 relays varying degrees of enthusiasm among reviewers for our proposal. Among the scientific community, there is a clear and growing interest in understanding the relevance of low-frequency HIV-1 drug resistance, and a few studies have been presented or published since the last submission [2-6]. However, the aims of this application remain highly novel. In fact, the editors' summary and the editorial by [name] that accompany the most recent publication on this topic state "It remains to be determined if the prevalence of these presumably transmitted mutations will wane with time" and "…because data on minority drug-resistant viruses are limited, more studies - particularly with recent populations - are needed before testing for these variants can be considered appropriate in the clinical management of newly diagnosed HIV infection" [5, 7]. We concur. These are exactly the studies proposed in Aims #1 and #2 of this application.

It was "unclear to reviewers whether the body of data that would be produced by this study would be able to alter treatment of people who are acutely infected with HIV."

Although our data would not answer the question whether ARV therapy should be initiated during acute HIV-1 infection, it will help to answer other questions relevant to the care of persons with acute HIV-1 infection. If low-frequency mutations negatively impact the response to ARV therapy, use of more-sensitive assays should be considered at the time of HIV-1 diagnosis. If low-frequency mutations negatively impact the response to ARV therapy but this effect is attenuated by an increasing time interval between HIV-1 acquisition and the start of ARV therapy, treatment during acute HIV-1 infection should be deferred (given that the current data show no clear benefit of immediate treatment on long-term clinical outcomes).

"Reviewers are interested and excited about aim three, the partner study, but want to know the proportion of subjects that present with drug resistance mutations acquired from their partner."

We share the enthusiasm of the reviewers regarding Aim #3. While this is a particularly exciting area of our research, it is important to note that this analysis is inextricably linked to the other project aims. For example, because we cannot study partners at the exact moment of HIV-1 transmission, it is essential for us to determine the duration that low-frequency mutations are detected over time following HIV-1 acquisition (Aim #1). If the source and recipient partners do not have the same pattern of drug resistance mutations, data on the "persistence" of low-frequency mutations (i.e. whether the "prevalence of these presumably transmitted mutations will wane with time") will help us estimate whether the different patterns we observe were actually due to the lack of transmission of mutant virus from the source to recipient partner or due to the overgrowth of the low-frequency mutations by wild-type viruses in the recipient partner in the interval between HIV-1 acquisition and study enrollment.

At the recommendation of reviewers, we have deferred this resubmission until our pilot project was completed; the findings are not significantly different from what we previously described. The overall prevalence of transmitted HIV-1 drug resistance is somewhat lower (34% versus 46%) because subjects were studied in reverse chronologic order, and those recently studied were among those enrolled prior to 2000. However, we remain confident that the primary objectives of each of the aims will be sufficiently powered with continued enrollment of subjects with acute HIV-1 infection and their putative source partners during a planned five-year study period, as described in detail in **5. Research Design and Methods.**

Other concerns of reviewers are addressed below. Changes to the submission are indicated by italicized text.

Critique #1:

1. "…the proposed research … would not likely affect treatment options of HIV infected individuals." and "Most importantly, is this study relevant to clinical significance as patients can be diagnosed to be in virological failure and function normally with the diagnosis of acute HIV infection."

As mentioned above, results from these studies could modify current treatment practices. We agree with Reviewer #1 that low-frequency mutations may not, in fact, uniformly reduce the efficacy of ARV therapy, and there may be negative consequences if clinicians unnecessarily avoid effective ARV agents in favor of more complicated regimens. It also should be determined, even if low-level mutations are clinically relevant, if use of more-sensitive HIV-1 drug resistance assays prior to initiation of ARVs would be cost-effective.

We do not share the opinion of Reviewer #1 that virologic failure is of little consequence. Most experts would agree that it is not advisable to allow persons on ARVs to experience virologic failure. Individuals who acquire HIV-1 infection in 2008 are predicted to live for decades following infection, much of the time while receiving ARV therapy. Although several highly effective agents from different ARV classes were recently approved, the rapid development, for example, of the M184V mutation completely eliminates the ability to construct a standard-of-care ARV regimen that is once-a-day and easily tolerated. Increasing pill burden, dosing frequency, and/or increased medication side effects from subsequent regimens would reduce adherence and the chance of virologic success. Thus the initial virologic failure is not without long-term consequences, whether it is in acute or established HIV-1 infection.

2. "The partner studies proposed … addresses an important area of research, but the number of subjects studied to [date] is small and it is still unclear whether [there will be] an adequate number of subjects to adequately power the studies."

In **5.c.3** we explain in detail how the combination of our recruitment record, the likelihood of confirming putative partners, and the likelihood that source partners would have HIV-1 drug resistance will achieve a sample size that has adequate power for the proposed analyses. "… we will have 82% power to detect a transmission probability of all source partner mutations of 80% or less if we have 17 confirmed partner-pairs in which the source partner has at least one HIV-1 drug resistance mutation…" We would need to enroll 0-21 putative source partners in order to have a total of 17 confirmed partner-pairs in which the source partner has at least one drug resistance mutation. Notably, three partner-pairs have enrolled in the last six months. With continued enrollment, we will have enrolled the maximum number of needed partner-pairs by the end of year five.

3. re: Aim 1: "It is unclear how the determination that low-frequency mutations are rapidly lost to detection would support drug resistance testing at the time of entry into care."

Guidelines currently recommend HIV-1 drug resistance testing at the time of entry into care [8] even though transmitted mutations detected by consensus sequencing continue to be detected for years following HIV-1 acquisition [9]. HIV-1 surveillance activities of Public Health - Seattle & King County incorporate resistance testing into the care continuum at an even earlier time point, using remnant sera from the initial positive HIV-1 antibody test for consensus sequencing. Results are then communicated to providers of clinical care. If data indicate that low-frequency HIV-1 drug resistance mutations are clinically relevant and are rapidly lost to detection and if more-sensitive assays are developed for clinical use, our public health activities might be tailored to look for low-frequency mutations instead of mutations detected by consensus sequencing.

4. "Also, the PI is urged to be creative in obtaining more subjects since power is a question."

Details in **5. Research Design and Methods** explain that all of the primary objectives are adequately powered with the anticipated sample size. Depending on results of these studies, future grant applications could, for example, generate collaborations with other cohorts of partner-pairs in order to study the transmission of specific mutations (e.g. K103N) in greater depth.

5. "Specifically, the public health importance of the data that would be obtained is still not clear."

In our view, the proposed studies are highly relevant to public health and represent an interface between public health and HIV-1 clinical research and care. Explicitly, if more-sensitive assays are endorsed without a better understanding of the impact of low-frequency mutations (Aim #2), the detection of minority variants might lead care providers to avoid prescribing the convenient first-line ARV regimens that have fewer pills and less-frequent dosing. A greater complexity of ARV regimens could reduce patient adherence and lead to a paradoxical increase in the prevalence of drug resistance. If minority variants are clinically relevant, knowing the duration that these mutations may be detected (Aim #1) would support recommendations for HIV-1 drug resistance testing at entry to care and should lead public health departments to consider incorporating drug resistance testing into HIV-1 confirmatory testing and public health surveillance programs [10]. Furthermore, understanding the true prevalence of resistance to different classes of ARV medications would help care providers to select appropriate empiric ARV regimens for post-exposure prophylaxis (PEP) or for the treatment of acute HIV-1 infection."

Critique #2

1. "Although the oligonucleotide ligation assay (OLA) is more sensitive than consensus assays, there are several novel assays which can detect variants at a frequency of 1% of less. The rationale for using the OLA assay - that more sequences can be sampled - is undercut by the central question of the application - the import of transmitted minor variants over time in the newly infected patient."

We agree with Reviewer #2 that there are other more-sensitive assays, but polymorphisms hamper these assays to a greater degree than OLA. Furthermore, extremely sensitive assays may at times be so sensitive as to detect the low background levels of random mutations that were described in HIV-infected populations even prior to the first use of ARVs in the 1980's. For this reason, although the real-time PCR assay used by Johnson et al [5] can detect HIV-1 drug resistance in as little as 0.001% of the viral quasi-species, the authors used cut off levels between 0.4-2.0% (similar to the sensitivity of OLA) for their analyses.

Critique #3

1. "While history of exposure to PrEP or PEP is a very important variable, exclusion of these subjects may be an error, particularly if these prevention modalities become commonly used."

Although PEP and PrEP have been used by a limited number of individual providers, ongoing randomized clinical trials (RCTs) have just begun and widespread adoption is likely several years away if these RCTs show positive results and funding can be identified for implementation. At the suggestion of this reviewer, we will plan to enroll and study these subjects, but we will analyze their data separately.

2. "A biohazard comment was noted in the prior critique and a description continues to be lacking."

We believe that Reviewer #3 refers to a prior comment by Reviewer #2. Additional text was added to **7.b.2 Protection against risk** documenting the biohazard training that clinical and laboratory staff receives. Further details on this training and procedures are available through the UW Biosafety Manual (online at: http://www.ehs.washington.edu/rbsbiosafe/sectioniv.pdf)

3. "…the study section believes that the focus on aim 3 should be able to be completed in 3 years and recommend that the time and budget be reduced to 3 years."

As outlined in **5.g Timetable for all projects**, the laboratory work to be performed for this project will commence with specimens identified for Aim #3, and preliminary results are likely to be generated within the first two years. However, because the additional sample size for all aims will require additional enrollment, shortening the proposal to fewer than five years is not feasible and risks the success of these studies.

Public health surveillance programs using consensus sequencing (genotyping) estimate that at least one in ten antiretroviral (ARV)-naïve persons infected with HIV-1 in the United States acquires drug resistant HIV-1. Guidelines therefore recommend resistance testing at the time of entry into care. However, consensus sequencing cannot detect low-frequency variants at levels below 10-50% of the viral population. The oligonucleotide ligation assay (OLA) is a more-sensitive assay that can detect mutations occurring in as little as 5% of the viral quasi-species. In a pilot study conducted among subjects with primary HIV-1 infection enrolled at the University of Washington Primary Infection Clinic (PIC), consensus sequencing detected transmitted HIV-1 drug resistance in *6% of 100* subjects, and OLA detected low-frequency mutations in *28 (30%) of 94* subjects who did not have mutations identified by consensus sequencing.

We propose studies that will use OLA to address questions pertaining to the transmission and subsequent consequences of HIV-1 drug resistance. In **Aim #1**,we will study ARV-naïve PIC subjects to compare the duration of detection ("persistence") and level of detection of transmitted HIV-1 drug resistance over time in peripheral blood mononuclear cells (PBMCs), blood and seminal plasma. In **Aim #2**, we will study PIC subjects initiating ARV therapy and use OLA to determine whether additional mutations can be detected in PBMCs during successful treatment due to the selection of transmitted low-frequency drug resistance mutations or the development of new mutations. In **Aim #3**, we will use OLA to compare HIV-1 drug resistance patterns in PIC subjects and their source partners to determine whether HIV-1 drug resistance impacts "transmission fitness".

These novel investigations would broaden our understanding of the natural history and clinical impact of low-frequency HIV-1 drug resistance and inform guidelines for the testing and treatment of HIV-infected persons. If more-sensitive HIV-1 drug resistance assays were to be endorsed for clinical care before there is a full understanding of the relevance of low-frequency mutations, the potential increase in the complexity of initial ARV regimens and subsequent reduction in patient adherence could paradoxically increase the prevalence of drug resistance. Finally, empiric data from partner-pairs will generate information on correlates of HIV-1 transmission that could be incorporated into future models of the population dynamics of drug resistance. These models would estimate the overall proportion of HIV-1 drug resistance that is transmitted from ARV-naïve source partners with primary HIV-1 infection versus ARV-experienced source partners with established HIV-1 infection. This data could be used to design public health interventions targeted to these populations to reduce the spread of transmitted HIV-1 drug resistance.

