The continued detection (sometimes called "persistence"*)* of HIV-1 drug resistance mutations over time is also likely to be associated with viral fitness. In acquired HIV-1 drug resistance, mutations that impair viral fitness are quickly overgrown by wild-type virus after the removal of ARV selection pressures [79]. In contrast, the *fourteen* subjects described in the analysis above who were infected with mutant viral variants that had *median RC of 72%* at baseline were followed longitudinally for a median of *108 (range 15-226) weeks*; the mutant variant was lost to detection by consensus sequencing in only one subject *148 weeks* following HIV-1 infection [9]. Others have also found that transmitted HIV-1 drug resistance mutations identified by consensus sequencing can be detected in PBMCs, blood and seminal plasma for years after HIV-1 infection [17-25]. However, we are unaware of published data that have systematically evaluated the detection of low-frequencyHIV-1 mutations in plasma and PBMCs over time in subjects with primary HIV-1 infection. It is likely that the same factors (e.g. low fitness) that result in the presence of transmitted HIV-1 drug resistance at low levels following HIV-1 acquisition would continue to affect the relative growth of viral variants in the absence of ARV therapy. With time, levels of low-frequency viral variants could fall below the limits of detection of even the most sensitive drug resistance assays. Further understanding of the dynamics of low-frequency HIV-1 drug resistance in different compartments will help guide recommendations for the timing and selection of HIV-1 drug resistance assays to maximize the identification of transmitted HIV-1 drug resistance.

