**4.g Transmitted HIV-1 drug resistance among subjects enrolled in the PIC Cohort study**

A New Investigator Award from the UW Center for AIDS and STD to [name] provided supplemental funding to SeaPIP for a pilot project to evaluate the prevalence and impact of transmitted low-frequency HIV-1 drug resistance in subjects with primary HIV-1 infection. Consensus sequencing and OLA were performed on the first available plasma and PBMC specimens from ARV-naïve subjects enrolled in the UW PIC cohort between 1996 and 2005. Subjects were preferentially selected for study if they had enrolled in the cohort within 30 days of HIV-1 infection or if they initiated ARV therapy during follow-up. Demographic and other characteristics of subjects were otherwise similar to the entire PIC cohort.

*Baseline resistance test results are available from 100 subjects tested to date. Consensus sequencing and OLA were performed using stored frozen plasma and PBMCs obtained a median of 29 (IQR 19-66) and 30 (IQR 19-66) days after HIV-1 infection, respectively. Consensus sequencing detected transmitted HIV-1 drug resistance in 6 (6%) of 100 subjects, and OLA detected low-frequency mutations in 28 (30%) of the 94 subjects who had no mutations detected by consensus sequencing. OLA identified significantly more subjects with transmitted resistance in both plasma and PBMCs compared to consensus sequencing (****Table 4****).*

**Table 4: Number of ARV-naïve subjects with transmitted** HIV-1 drug resistance at baseline

| **4a:** OLA v consensus sequencing in plasma | | | |
| --- | --- | --- | --- |
|  | | OLA | |
| - | + |
| sequencing | - | 74 | **21** |
| + | **0** | 5 |

| **4b**: OLA v consensus sequencing in PBMCs | | | |
| --- | --- | --- | --- |
|  | | OLA | |
| - | + |
| sequencing | - | 78 | **16** |
| + | **2** | 4 |

| **4c**: consensus sequencing in plasma v PBMCs | | | |
| --- | --- | --- | --- |
|  | | PBMCs | |
| - | + |
| plasma | - | 94 | **1** |
| + | **0** | 5 |

| **4d:** OLA in plasma v PBMCs | | | |
| --- | --- | --- | --- |
|  | | PBMCs | |
| - | + |
| plasma | - | 66 | **8** |
| + | **14** | 12 |

+ = subjects w/ ≥1 mutation or mixture.

- = subjects w/o mutations or w/ indeterminate results

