**5.b Study objectives**

**Aim #1: Determine whether the "level" of detection of HIV-1 drug resistance variants predicts the duration of detection of these variants over time since HIV-1 acquisition.**

Primary objectives:

1) Quantify the proportion of subjects with transmitted HIV-1 drug resistance that have mutations that remain detectable in PBMCs compared to blood plasma 6 and 12 months after HIV-1 infection.

2) Compare the proportion of subjects with low-frequency HIV-1 drug resistance that have mutations that remain detectable 6 and 12 months after HIV-1 infection compared to subjects with mutations detected by consensus sequencing at baseline.

Secondary objectives:

1) Identify subject characteristics associated with transmitted low-frequency HIV-1 drug resistance.

2) Compare the detection of mutations in blood and seminal plasma in male subjects over time.

3) Describe differences in the detection of specific drug resistance mutations (e.g. M184V) over time.

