**5.c Study design and data analysis**

**5.c.1 Aim #1: Determine whether the "level" of detection of HIV-1 drug resistance variants predicts the duration of detection of these variants over time since HIV-1 acquisition.**

Aim #1 will evaluate *the level* of detection of low-frequency HIV-1 drug resistance mutations in PBMCs, blood and seminal plasma from ARV-naïve subjects at baseline and over time. Because we anticipate that no more than 50% of male subjects will provide semen specimens and we will have few female subjects available for study, the study will be powered to compare transmitted HIV-1 drug resistance in PBMCs and blood plasma. We hypothesize that a smaller proportion of subjects will have low-frequency mutations that remain detectable compared to subjects with mutations detected by consensus sequencing at baseline, and a greater proportion of subjects will have mutations that remain detectable in PBMCs compared to blood and seminal plasma.

All subjects selected for study will have baseline testing to detect transmitted HIV-1 drug resistance using both OLA and consensus sequencing. Results of baseline testing will be combined with results from our pilot study to obtain a more precise estimate of the prevalence of transmitted HIV-1 drug resistance in Seattle. Logistic regression analyses will explore subject characteristics potentially associated with transmitted drug resistance including subject age; race/ethnicity; level of education; risk factor for HIV-1 acquisition; year of HIV-1 acquisition; use of methamphetamine, other illicit drugs, or erectile dysfunction medications; number of recent sex partners; and locations for meeting new partners (e.g. bathhouses, internet, etc) [188, 189].

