**Table 8: Estimated number of subjects with mutations in PBMCs and plasma over time**

| **8a**: Distribution of subjects at baseline | | | |
| --- | --- | --- | --- |
|  | | plasma | |
| - | + |
| PBMCs | - |  | *14 (41%)* |
| + | *8 (24%)* | *12 (35%)* |

| **8b**: Distribution of subjects at follow-up | | | |
| --- | --- | --- | --- |
|  | | plasma | |
| - | + |
| PBMCs | - | 12 (30%) | 4 (10%) |
| + | 18 (45%) | 6 (15%) |

| **8b**: Distribution of subjects at follow-up | | | |
| --- | --- | --- | --- |
|  | | plasma | |
| - | + |
| PBMCs | - | *20 (25%)* | *16 (20%)* |
| + | *40 (50%)* | *4 (5%)* |

+ = subjects w/ ≥1 mutation or mixture.

- = subjects w/o mutations or w/ indeterminate results

**Table 8**: The number of subjects who would have transmitted drug resistance identified in PBMCs and plasma at follow-up (**Table 8b and 8c**) was estimated for power calculations *based on the distribution of mutations identified at baseline (****Table 8a****) from the pilot project.*

Power calculations were performed using a two-sided McNemar's exact test with significance level of 0.05. We assumed that the baseline distribution of subjects with mutations in PBMCs, plasma, or both would be similar to that found in the pilot study *(****Table 8a):*** *25% in PBMCs, 40% in plasma, and 35% having mutations in both PBMCs and plasma).* In these power calculations, we estimated the proportion of these subjects who would have mutations detected in PBMCs and/or plasma *at the* follow-up *evaluation* (**Table 8b and *8c***). If *mutations initially detected in PBMCs and plasma remain detectable in 100% and 25% of subjects, respectively, in the follow-up specimen,* 30% of subjects who had transmitted HIV-1 drug resistance *will* no longer have detectable mutations, 10% of subjects *will* have mutations detected in plasma only, 45% of subjects *will* have mutations detected in PBMCs only, and 15% of subjects *will* continue to have mutations detected in both PBMCs and plasma (***Table 8b***). *With this distribution,* we would have 84% power to determine whether a significant difference exists in the detection of mutations in PBMCs versus plasma over time with 40 subjects who had transmitted HIV-1 drug resistance detected at baseline.

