*If the difference in loss of detection between PBMCs and plasma is less extreme, and 67% and 13% of mutations initially detected in PBMCs and plasma remain detectable in follow-up (****Table 8c****), then we would have 89% power to determine whether a significant difference exists in the detection of mutations in PBMCs versus plasma over time with 80 subjects who had transmitted HIV-1 drug resistance detected at baseline. Note that the McNemar's exact test takes account only of the distribution at follow-up and not changes over time; these calculations are therefore extremely conservative compared to the planned analysis described below.*

This sample size will be generated from previously enrolled subjects and from new enrollment. *There are 73 subjects among the entire PIC cohort who enrolled within 30 days of HIV-1 infection, who enrolled after 1996, and who have a median of 36 (range 0-139) months in follow-up.* Nine subjects studied through the pilot project were enrolled within 30 days of HIV-1 infection, had at least one low-frequency mutation identified, and have at least one year of follow-up in the cohort without ARV treatment. *Fifty-four subjects have enrolled in the cohort since the end of the pilot project, and we* anticipate that there will be an additional *15* subjects who will enroll before the start of this project, all of whom *will have been* enrolled within 30 days of HIV-1 infection. If we assume that *34*% of these subjects would have HIV-1 drug resistance mutations and *66% will remain ARV-naïve and in follow-up for at least one year*, we would expect that *15 previous-enrolled subjects will be eligible for study in Aim #1*. Prospective enrollment of *16* subjects with transmitted HIV-1 drug resistance in addition to the *24* previously-enrolled subjects would achieve the desired total sample size of 40. If *34*% of newly-enrolled subjects have transmitted HIV-1 drug resistance but *33*% of subjects initiate ARVs within 30 days after HIV-1 diagnosis, we would need to enroll *72* subjects by the end of the project period to achieve this sample size *(****Figure 5****).* Given our rate of enrollment in recent years, this number would be reasonably expected to accrue within the five years of the project.

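### The statement that all primary objectives are adequately powered is not supported for Aim 1 primary objective 2, which on the pilot split would rest on about 5 to 7 consensus-positive subjects

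*Protocol*

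**What the plan says.** Section 1 makes the claim twice. The reply to Critique #1, item 4, says the methods section will "explain that all of the primary objectives are adequately powered with the anticipated sample size", and the opening of the reply expresses the same confidence about the primary objectives of each aim.

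Section 5.b lists two primary objectives for Aim 1. The first compares PBMCs with blood plasma. The second is to "Compare the proportion of subjects with low-frequency HIV-1 drug resistance that have mutations that remain detectable 6 and 12 months after HIV-1 infection", with subjects whose mutations were found by consensus sequencing at baseline as the comparison group.

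Section 5.c.1 is explicit about what was sized: "the study will be powered to compare transmitted HIV-1 drug resistance in PBMCs and blood plasma". The method is a "two-sided McNemar's exact test with significance level of 0.05", and for 40 subjects with baseline resistance the result is "we would have 84% power to determine whether a significant difference exists in the detection of mutations in PBMCs versus plasma over time". A second scenario gives 89% with 80 subjects, but the accrual plan aims for 40. The planned analysis is a GEE logistic model that adjusts for the compartment and the level of detection at baseline. The low-power caveats in 5.c.1, 5.c.2 and 5.f.4 concern semen, specific mutations and virologic failure. None covers objective 2.

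**The concern.** Objective 2 compares two groups of subjects, so its information is limited by the smaller group. The pilot suggests that this group is very small: "Consensus sequencing detected transmitted HIV-1 drug resistance in 6 (6%) of 100 subjects", against 28 subjects with mutations found only by OLA. The paired calculation for objective 1 says nothing about this contrast.

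Objective 2 carries half of the Aim 1 hypothesis, namely that low-frequency mutations are lost faster, and the public-health implication drawn from it in section 2. If the groups are as small as the pilot suggests, a non-significant result could easily be read as similar persistence when the study could not have shown a difference of moderate size. The adequacy claim invites that reading.

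**Working it through.** **1. The plan's own figures.** Objective 1 was recomputed as unconditional exact McNemar power, with the number of discordant pairs binomial(n, sum of the discordant cells) and a two-sided exact binomial test at 0.05.
- 40 subjects, discordant cells 45% and 10%: 84.4% (stated 84%).
- 80 subjects, discordant cells 50% and 20%: 88.9% (stated 89%).

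Both reproduce. Objective 2 has no stated figure to reproduce.

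**2. Expected group sizes for objective 2.** Inputs: 6 consensus-positive and 28 OLA-only pilot subjects (4.g); target 40, made up of 24 previously enrolled and 16 new (5.c.1).
- Consensus share: 6/(6 + 28) = 17.6%. Expected number: 40 × 6/34 = 7.1.
- Nine of the 24 are counted on this basis: "Nine subjects studied through the pilot project were enrolled within 30 days of HIV-1 infection, had at least one low-frequency mutation identified". If these nine are all consensus-negative (an assumption), the expected number is (40 − 9) × 6/34 = 5.5.
- The comparison is therefore about 5–7 against 33–35.
- Sensitivity: with the 11% Seattle consensus prevalence (section 2) over the 34% overall prevalence, 40 × 0.11/0.34 = 12.9, or 31 × 0.11/0.34 = 10.0.

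**3. Retention assumptions.** The protocol gives none for objective 2.
- Consensus group: 13/14 = 93%, from the cited study of fourteen subjects in section 3.c, where "the mutant variant was lost to detection by consensus sequencing in only one subject". 100% is used as a sensitivity value.
- Low-frequency group: 50% as an illustration, and the value implied by Table 8b. There, 12 of 40 subjects lose all mutations, so 28 keep at least one. With n consensus subjects at retention p, the implied low-frequency retention is (28 − n·p)/(40 − n). For n = 5, 6, 7 and p between 93% and 100% this is 64–67%.

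**4. Power, detection in any compartment.** Two-sided Fisher exact test at 0.05, by full enumeration:

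| Consensus vs low-frequency retention | 5 vs 35 | 6 vs 34 | 7 vs 33 |
|---|---|---|---|
| 13/14 vs 50% | 26% | 37% | 50% |
| 13/14 vs 60% | 4% | 10% | 19% |
| 13/14 vs 64% | 1% | 4% | 10% |
| 100% vs 50% | 37% | 57% | 76% |
| 100% vs 64% | 2% | 7% | 17% |

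For 80% power, low-frequency retention must be roughly 30–38% or less when consensus retention is about 93%, or about 40–48% or less when it is 100%.

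A normal approximation is kinder. It gives 40%, 50% and 58% at 93% vs 50%, and 15% to 44% at 64% with consensus retention of 93–100%. It reaches 80% and 87% for 6 and 7 subjects at 100% vs 50%, but it is unreliable with so few subjects and a rate at the boundary.

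**5. A check that assumes no consensus losses.** If every consensus subject keeps a mutation, Fisher significance needs at most 16/35, 17/34 or 18/33 low-frequency subjects to keep one. Table 8b then implies 28 − 5 = 23, 28 − 6 = 22 or 28 − 7 = 21. The result that the plan itself expects would not be significant.

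**6. By compartment, under Table 8b, with consensus retention 13/14.**
- PBMCs: 24 of 40 positive at follow-up. Power is about 11% to 40% for 5 to 7 consensus subjects.
- Plasma, all 40 as denominator: 10 of 40 positive. Power is 97% or more.
- Plasma, only the 30 subjects (75%) expected to be plasma-positive at baseline, with 4, 5 or 6 of them consensus-positive: implied low-frequency retention is (10 − n × 13/14)/(30 − n) = 24%, 21% or 18%, and power is 81%, 92% or 96%. At a flat 25% it is 79–89%.

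**7. Larger consensus group.** With 10 or 13 of 40, power at 13/14 vs 50% is 69% or about 77%. With 13 it is 41% at 64%.

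**The case against.** The strongest reply is that the size of the shortfall depends on rates and a readout that the protocol does not fix. Objective 2 names no compartment. Table 8b assumes heavy loss from plasma, and a plasma readout would then have about 80% power or more even with this few consensus subjects. The aim also supposes that low-frequency mutations may disappear quickly, so retention of 30% or less is not excluded. The 13/14 comes from consensus sequencing over a median of 108 weeks; OLA at 6 and 12 months could find more, which would raise power. The pilot share is itself one estimate, from 1996–2005 enrollees who were preferentially selected. All of this stands. It is why the claim should be called unsupported.

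A reader might infer that the claim is false, or that objective 2 is underpowered under any reasonable assumption. The document does not support that, because the plasma readout is a counterexample built from its own planning figures.

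A reader might also infer that the primary analysis must be replaced by a regression on baseline OLA level. That is not needed: section 2 and the GEE model in 5.c.1 already provide for it. Since consensus sequencing misses variants below 10–50% of the population, the higher level categories are likely to be sparse too.

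Two defences carry little weight. The 80-subject scenario would give about 14 consensus subjects (80 × 6/34), with 53% power at 93% vs 64% and 91% at 93% vs 50%, but accrual aims for 40. The GEE model uses repeated measures but adds no consensus-positive subjects.

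**Conclusion.** The adequacy statement in section 1 has no support in section 5 as far as Aim 1 primary objective 2 is concerned. The only Aim 1 calculation, which is correct, is for objective 1.

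On the pilot split the consensus group would be about 5–7 of 40, or about 10–13 on the Seattle figure. Read at subject level for any compartment, with the 5–7 subjects, power falls well short of 80%: about 26–50% at 50% low-frequency retention and about 1–10% at the roughly 64% implied by Table 8b. PBMCs alone are also short. Among the Table 8b readouts, only plasma alone reaches about 80%.

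The group sizes follow from the protocol's own numbers, except that the lower one treats the nine pre-selected pilot subjects as consensus-negative. The power figures also rest on the 13/14 borrowed from the cited study and on the choice of Fisher's test. This should be corrected as a statement about power. It does not show that the design or the objective must be dropped.

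**What to change.** - In both places in section 1, limit the adequacy claim to the objectives for which section 5 gives a calculation.
- In 5.c.1, state the expected group sizes for objective 2 (about 5–7 vs 33–35 on pilot figures, with the 10–13 sensitivity), and its power or confidence-interval width for PBMCs, plasma and any compartment under stated retention assumptions.
- Report the low-frequency versus consensus contrast with exact confidence intervals, so that a null result is not read as no difference.
- Name the GEE model with baseline level, already planned in 5.c.1, as the supporting analysis.

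This is a change of wording and reporting. It needs no new subjects or assays. The downside is that the application must present a less favourable power statement for objective 2.
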